### Measurement sessions

#### AFO scanning and fitting

When a patient is recruited to the study they will be randomised and assigned to one arm of the study. The appropriate orthotist will scan them for a rigid AFO and deliver the AFO according to the set of design criteria unique to this study. After scanning and prior to AFO fitting and tuning, the baseline measures can be taken.

#### Baseline

All patients will have baseline gait measurements taken using a 3D motion analysis system. After measurements have been taken, patients in the intervention arm will additionally be shown relevant visualisations which will help to explain and quantify their gait problems.

#### Tuning

Patients in the intervention arm will be given AFO tuning with visualisation. Patients in the non-intervention arm will be given AFO tuning using observational techniques. All patients will have gait measures taken at the end of the tuning process, wearing their tuned AFO.

#### Outcome measures (3 months)

All patients will have 3 month gait measurements taken using a 3D motion analysis system. Patients in the intervention arm will have their progress discussed, aided by visualisations of the data measurements just taken.

#### Follow-up measures (6 months)

All patients will have 6 month gait measurements taken using a 3D motion analysis system. Patients in the intervention arm will have their progress discussed, aided by visualisations of the data measurements just taken.

### Participant recruitment (inclusion/exclusion criteria)

The stroke physiotherapy team will identify stroke patients who are suitable for AFO treatment and will notify the researcher of those considered to meet all of the inclusion/exclusion criteria (see Table 1). The researcher will then inform them of the study and if they are interested they will be given a copy of the 'information for participants' sheet to read. The patient will be given a suitable amount of time (minimum of 48 hours) to consider volunteering. During this time they will be free to ask for more information from the researcher about the study and to consult with friends, carers or relatives.

**Table 1 T1:** Participant inclusion and exclusion criteria

Inclusion criteria	Exclusion criteria
Inpatients who have suffered a recent (1-12 months) hemiplegia	Are unable to give informed consent
Aged 16-80 years	Are unable to walk, even when assisted
Male or Female	Suffer from significant peripheral vascular disease ? not suitable for fitting of AFO
Have difficulty walking, but able to walk with/without assistance	Have any other significant medical problems likely to preclude use of AFO or follow-up
Have difficulty flexing knee and extending hip during walking	
Meet the criteria for AFO referral as outlined in AFO screening tool (NHS BPS, Appendix 9)	
Able to give informed consent	
Able to attend for follow-up at 3 and 6 months	

Communication problems are common in stroke patients, so the patient's care team will be asked to assess the patient's capacity for making informed consent. In addition to providing the 'participant information' sheet the care team will also take the time to verbally explain the trial to the patient if required. It will be made clear to the patient that treatment will not be withheld if they decline to participate in the trial. They will still receive an AFO and an AFO tuning session if they do not volunteer. If they agree to participate in the trial they will be asked to sign a 'research participant consent form'. Should the patient be unable to sign or to mark a document so as to indicate his/her consent, it can be given orally in the presence of at least one witness and recorded in writing. Suitable verbal and graphical explanations will supplement the consent process as necessary on an individual basis. The 'information for participants' sheet makes it clear that the patient is free to withdraw from the study at any time, without giving reason and that withdrawal will not their standard of care nor their future treatment.

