**Figure 1 F1:**
[figure not shown]
**Flow diagram of trial design showing intervention (visualisation) and non-intervention (observation) arms**.

The randomisation sequence will be generated using an independently verified S-PLUS program, by the method of randomised permuted blocks of length four, with participants allocated to interventions in a 1:1 ratio. Researchers will access the random allocations via the study web portal (designed and maintained by The Robertson Centre for Biostatistics at The University of Glasgow) and the sequence will remain concealed until the participant's details are registered on the system.

As patients are recruited to the trial they will be randomly allocated to one of two multidisciplinary teams (MDTs). Each of these MDTs will be made up of a physiotherapist, orthotist and bioengineer. MDT-A will administer the intervention arm of the study, MDT-B will administer the non-intervention arm. In the intervention arm patients will be shown visualisations of their gait patterns and progress throughout the trial. Additionally, the clinicians in MDT-A will also be able to use the gait data and visualisation software to aid their clinical decision making during the AFO tuning session. MDT-B will conduct AFO tuning using standard observational techniques.

Baseline, outcome (3 months) and follow-up (6 months) measurement sessions will be collected by the bioengineer and a third physiotherapist who is independent of the MDTs.

All clinical decision making will be carried out by the physiotherapists and orthotists, while the bioengineer will play a purely technical role collecting data and presenting it to the clinicians and the patient when it is required. The same bioengineer will be used in both MDTs and will be present during all sessions.

Ideally both MDTs would be identical, but this is clearly not possible. Two different MDTs are needed to avoid learning effects in the intervention arm of the study crossing over to the non-intervention and confounding results. In order to balance the MDTs, team members will be selected such that they have similar levels of experience and they will all be required to complete a small amount of basic biomechanics refresher training before the trial commences.

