### Sample size (power calculation used)

The sample size was decided upon by using data from previous similar studies. A clinically relevant change in walking velocity has been identified as 0.2 m/s [20]. Using conservative figures from a previous RCT [21] the standard deviation of the treatment effect in a control population was 0.24 m/s. This provided a standardised difference statistic of 0.831, which suggests that a sample size of 62 (31 per group) will give 90% power at 5% significance level. Seventy participants (35 per group) will allow for a withdrawal rate of > 10%.

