### Quantitative data collected (Primary and Secondary outcome measures)

The primary outcome measure for this study is walking velocity [22]. Secondary outcome measures include; lower limb joint kinematics (thigh and shank global orientations) & kinetics (knee and hip flexion/extension moments, ground reaction force FZ_2 _peak magnitude), step length, symmetry ratio based on step length [23], Modified Ashworth Scale [24], Modified Rivermead Mobility Index [25,26], EuroQol (EQ-5D) [27].

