### Statistical Analysis

Quantitative data from the four patient measurement sessions (baseline gait, AFO tuning, three and six month gait) will be analysed on an 'intention to treat' basis. Data will be held independently on a bespoke database at the Robertson Centre for Biostatistics at the University of Glasgow, and independent assessors comparing data sets will be blinded as to which arm of the trial each patient was allocated to.

The primary emphasis of the statistical analysis will be on between-group differences to establish if differences in outcome measures are apparent. This will be achieved using two-way repeated measures ANOVA analysis, followed by a series of post-hoc tests which are most likely to be t-tests.

All data will be tested for normality, and where normality does not occur the equivalent nonparametric tests will be used instead. A significance level of 0.05 will be used and a Bonferroni correction will be used when multiple t-tests are required. Qualitative data obtained from the various interviews will be collated and a suitable coding system established such that the responses can be categorised.

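### Time since stroke ranges from 1 to 12 months at entry but is used in neither the stated randomisation nor the stated analysis, which leaves avoidable variance and exposure to chance imbalance

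*Protocol article*

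**What the plan says.** All statements are in the protocol article.

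- **Eligibility** (Participant recruitment, Table 1): "Inpatients who have suffered a recent (1-12 months) hemiplegia".
- **Randomisation** (Study design, text after Figure 1): the sequence is generated "by the method of randomised permuted blocks of length four, with participants allocated to interventions in a 1:1 ratio". No stratification factor is named.
- **Timing** (same section): "Baseline, outcome (3 months) and follow-up (6 months) measurement sessions". A further gait measurement is made at the tuning session.
- **Primary outcome** (Quantitative data collected): "The primary outcome measure for this study is walking velocity".
- **Analysis** (Statistical Analysis): between-group differences are the main interest. "This will be achieved using two-way repeated measures ANOVA analysis, followed by a series of post-hoc tests which are most likely to be t-tests". No covariate is named.
- **Sample size**: "A clinically relevant change in walking velocity has been identified as 0.2 m/s", and "the standard deviation of the treatment effect in a control population was 0.24 m/s". This leads to 31 per group for 90% power at the 5% level, raised to 35 per group for withdrawals.

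Time since stroke appears only as an entry criterion. Natural recovery is not discussed.

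**The concern.** A patient who enters 1 month after stroke is measured at roughly 4 and 7 months after it. One who enters at 12 months is measured at roughly 15 and 18 months. If walking velocity is still improving spontaneously in the first and has levelled off in the second, their changes over the trial differ for reasons unrelated to tuning.

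An analysis that ignores time since stroke leaves that difference in the error term. With about 35 patients per arm, the arms may also end up with unequal shares of early entrants, and the estimate then carries part of the recovery difference. The remedy needs no new data, because eligibility cannot be checked without knowing the time since stroke.

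**Working it through.** **1. The plan's own figure.** With a target of 0.2 m/s, SD 0.24 m/s, two-sided 5% and 90% power, n per group = 2 × (1.960 + 1.282)² × (0.24/0.2)² = 30.3, so 31. The stated standardised difference of 0.831 gives 30.4, also 31. The figure reproduces. A noncentral-t calculation gives 89.6–89.8% power at 31 per group, so there is little slack.

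**2. Assumptions.** The article gives no recovery rate by time since stroke and no distribution of entry times. I assume that early entrants gain 0.1, 0.2 or 0.3 m/s more than late ones over follow-up, and that 50% or 80% enter early.

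**3. Chance imbalance at 35 per arm.** The SD of the between-arm difference in the early share is √(2p(1−p)/35).

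- p = 0.5: √(0.5/35) = 0.1195; × 1.96 = 0.234, or ±23 percentage points.
- p = 0.8: √(0.32/35) = 0.0956; × 1.96 = 0.187, or ±19 points.

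Multiplying by the gap gives the 95% limit of the resulting shift:

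| Gap (m/s) | Shift, 50% early (m/s) | Share of 0.2 m/s | Shift, 80% early (m/s) |
|---|---|---|---|
| 0.1 | 0.023 | 12% | 0.019 |
| 0.2 | 0.047 | 23% | 0.037 |
| 0.3 | 0.070 | 35% | 0.056 |

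These are limits. A one-SD shift at p = 0.5 is 0.1195 × gap = 0.012, 0.024 or 0.036 m/s.

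**4. Variance, if the recovery spread is already inside the 0.24 m/s SD.** Share removed by adjustment = p(1−p) × gap²/0.24². Reduction in standard error = 1 − √(1 − share).

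| Gap (m/s) | Share, 50% early | SE cut | Share, 80% early | SE cut |
|---|---|---|---|---|
| 0.1 | 4.3% | 2.2% | 2.8% | 1.4% |
| 0.2 | 17.4% | 9.1% | 11.1% | 5.7% |
| 0.3 | 39.1% | 21.9% | 25.0% | 13.4% |

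**5. Power and type I error, if the spread is extra to 0.24 m/s.** Simulation with 62 patients, blocks of four, entry uniform over 1–12 months, the gap declining linearly from the earliest to the latest entrant, residual SD 0.24 m/s, and 10,000 runs per gap:

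| Gap (m/s) | Type I error, unadjusted | Power, unadjusted | Power, adjusted |
|---|---|---|---|
| 0.1 | 4.8% | 89.6% | 89.3% |
| 0.2 | 5.0% | 88.3% | 89.6% |
| 0.3 | 5.1% | 85.7% | 89.4% |

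Here the gap lies between the extremes of entry time, which is a milder spread than the two-group split in steps 3 and 4. With a 50:50 split of the same gap added to 0.24, the SD is √(0.0576 + 0.25 × gap²) = 0.245, 0.260 or 0.283 m/s. Normal-approximation power at 31 per group, Φ(0.2/(SD × √(2/31)) − 1.96), is then 89%, 86% or 79%, against 91% with no added spread.

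**The case against.** A reader might infer that unequal natural recovery biases the comparison, so that it could pass for a tuning effect or conceal one. The documents do not support that. Both arms are randomised concurrently from a concealed sequence, so recovery acts on both. Only chance imbalance can move the contrast, and the 5% test already allows for it: simulated type I error without adjustment stays at 4.8–5.1%. The article is right to rely on randomisation against confounding.

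Other objections:

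- **The size rests on assumed gaps.** This stands. No passage supports any particular recovery gap, and even the largest one gives a 95% limit of about a third of the target. Recruitment of inpatients from stroke wards also makes an even early/late split doubtful, hence the smaller 80% figures.
- **If the spread is inside 0.24 m/s, the sample size has already paid for it.** This also stands. Adjustment then adds precision beyond the planned 90% and repairs no shortfall. If the spread is extra, the gain is nil at the smallest gap and under 4 percentage points at the largest in the linear simulation.
- **Covariates and strata may be set out in a fuller document.** This stands in part. A separate analysis plan could add a covariate, and the silence alone is no fault. But the article does describe a method, and arm-by-session ANOVA followed by t-tests makes no use of time since stroke. The criticism is of that stated method.
- **The trial is described as exploratory and is ongoing.** A broad entry window is a legitimate choice in such a trial. That it is under way limits what can still be done about randomisation, but not about the analysis.

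**Conclusion.** The point holds as one of efficiency and robustness. Time since stroke varies from 1 to 12 months, is known for every patient, and goes unused in the randomisation and analysis as described. Validity is not at issue.

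The loss is unknown from the documents. Under assumed gaps of 0.1 to 0.3 m/s it runs from negligible to worthwhile: a chance shift of up to about 0.02–0.07 m/s with half entering early, and 4–39% of the variance (3–25% with 80% early) if the spread lies within 0.24 m/s. If it is extra, unadjusted power in the linear simulation is about 90%, 88% and 86%, against 89–90% adjusted. A sharp early/late split would cost more. Severity is minor to moderate.

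**What to change.** Before unblinding, prespecify time since stroke at entry, as a continuous variable, together with baseline velocity, as a covariate in the walking velocity analysis. Include the interaction of time since stroke with session. Take the between-arm contrasts at 3 and 6 months from that model in place of unadjusted t-tests. If a separate analysis plan already does this, bring the article's description into line with it.

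The cost is a few degrees of freedom. A linear term plus its interaction with four sessions uses 1 + 3 = 4. If the baseline session is moved from the outcomes to the covariates, three sessions remain and the term uses 1 + 2 = 3, plus those for baseline velocity. No extra patients, visits or data are needed.

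Stratifying the web-portal randomisation by time since stroke is optional. It can apply only to patients not yet randomised, needs a cut-point that the documents do not supply, and may add an incomplete block.

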### Sample size (power calculation used)

The sample size was decided upon by using data from previous similar studies. A clinically relevant change in walking velocity has been identified as 0.2 m/s [20]. Using conservative figures from a previous RCT [21] the standard deviation of the treatment effect in a control population was 0.24 m/s. This provided a standardised difference statistic of 0.831, which suggests that a sample size of 62 (31 per group) will give 90% power at 5% significance level. Seventy participants (35 per group) will allow for a withdrawal rate of > 10%.

### Location

Participants will be recruited from the stroke wards at the Southern General Hospital, Glasgow, UK. Baseline, tuning, 3 month and 6 month sessions will all take place at West of Scotland Mobility and Rehabilitation Centre (WestMARC) at the Southern General Hospital, Glasgow, UK.

### Data collection equipment

3D motion analysis will be carried out using and 8-camera Vicon 612 motion analysis system (Oxford Metrics, UK) in conjunction with 2 AMTI BP400600 force platforms.

### Quantitative data collected (Primary and Secondary outcome measures)

The primary outcome measure for this study is walking velocity [22]. Secondary outcome measures include; lower limb joint kinematics (thigh and shank global orientations) & kinetics (knee and hip flexion/extension moments, ground reaction force FZ_2 _peak magnitude), step length, symmetry ratio based on step length [23], Modified Ashworth Scale [24], Modified Rivermead Mobility Index [25,26], EuroQol (EQ-5D) [27].

### Qualitative data

The quantitative outcome measures of the RCT are not sufficient to answer all of the study's secondary research questions, so through the use of qualitative research methods it is anticipated that an enhanced understanding of the effects of using visualisations in AFO tuning can be acquired [28]. This part of the study will explore what effect the use of the visualisation tool has on the experiences and understanding of patients and clinicians involved in the study, as well as what effect it has on the patient-clinician interactions.

One-to-one semi-structured interviews will be conducted with all clinicians and patients both before and after their participation in the study.

Before the study, after they have consented to participate, all patients will be required to complete short (15 minute) interviews. The main focus of the questions will be on their expectations of the AFO process, their personal goals and their personal perception of their walking ability at the baseline stage. Clinicians will also complete slightly longer (30 minute) interviews which concentrate on how confident they feel about biomechanics, what they look for during observational gait analysis (are there any inter-disciplinary differences?), attitudes towards 3D motion analysis and perceived difficulties in communicating gait abnormalities to health professionals from other disciplines.

After their participation in the study all patients will complete 30 minute interviews, covering a range of topics including; patient-clinician communication, understanding of their treatment, motivation levels, personal goals achieved, impact of visualisations. Their personal perception of their walking ability will also be reassessed. Clinicians will also complete 45 minute interviews, which will investigate themes such as; evidence of enhanced understanding of biomechanics, team working, perceived benefits/drawbacks of using software and confidence in their clinical decision making.

### Statistical Analysis

Quantitative data from the four patient measurement sessions (baseline gait, AFO tuning, three and six month gait) will be analysed on an 'intention to treat' basis. Data will be held independently on a bespoke database at the Robertson Centre for Biostatistics at the University of Glasgow, and independent assessors comparing data sets will be blinded as to which arm of the trial each patient was allocated to.

The primary emphasis of the statistical analysis will be on between-group differences to establish if differences in outcome measures are apparent. This will be achieved using two-way repeated measures ANOVA analysis, followed by a series of post-hoc tests which are most likely to be t-tests.

All data will be tested for normality, and where normality does not occur the equivalent nonparametric tests will be used instead. A significance level of 0.05 will be used and a Bonferroni correction will be used when multiple t-tests are required. Qualitative data obtained from the various interviews will be collated and a suitable coding system established such that the responses can be categorised.

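### Baseline is analysed as one of four outcome sessions and the deciding term is not fixed; a baseline-adjusted 3-month contrast would secure the planned power at no cost

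*Protocol article*

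**What the plan says.** In the protocol article, Statistical Analysis defines the data as "Quantitative data from the four patient measurement sessions (baseline gait, AFO tuning, three and six month gait", to be analysed by intention to treat with the main emphasis on differences between the arms. The method follows: "This will be achieved using two-way repeated measures ANOVA analysis, followed by a series of post-hoc tests which are most likely to be t-tests". Tests are at 0.05, with Bonferroni when several t-tests are needed. No baseline covariate or change score is mentioned, and neither a deciding ANOVA term nor a deciding session is named.

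The section on AFO scanning and fitting places baseline before the orthosis is fitted and tuned. Under Study design, the 3-month session is called the outcome session and the 6-month session follow-up.

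Sample size (power calculation used) rests on one two-group comparison of walking velocity, with a relevant change of 0.2 m/s. It says that "the standard deviation of the treatment effect in a control population was 0.24 m/s" and concludes that "a sample size of 62 (31 per group) will give 90% power at 5% significance level".

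**The concern.** Baseline precedes treatment, so randomisation makes the expected arm difference there zero. Entering that session as a level of the response means that the ANOVA's group term averages one null session with three treated ones. A fixed benefit shrinks by a quarter, while the between-patient variance stays in the error term. The comparison that was sized for 90% power is not this one.

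The other route through the same ANOVA is the group-by-session interaction. It does use baseline as a reference, but a significant result says only that the arms' profiles differ somewhere. Direction, size and timing must then come from the Bonferroni t-tests, and these were not what was sized either.

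At stake is the chance of detecting and describing a true 0.2 m/s benefit with 62 to 70 patients. Walking velocity is already measured at baseline. Randomisation is in blocks of four with no stratification described, so chance baseline imbalance is possible, and the stated analysis does not say how it would be handled.

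**Working it through.** **Inputs from the documents.** Effect 0.2 m/s, SD 0.24 m/s, 31 per arm, two arms 1:1, 5% level, 90% power (Sample size); four sessions, one of them before treatment (Statistical Analysis; AFO scanning and fitting).

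**Assumptions.** The documents give no between-session correlation ρ, so I use a range. I also assume compound symmetry and a constant 0.2 m/s effect at tuning, 3 and 6 months. The planning SD can be read in two ways, and I run both:
- raw: the SD σ of one velocity measurement is 0.24;
- change: the SD of change is 0.24, so σ = 0.24/√(2(1−ρ)).

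**Step 1: the plan's own figure.** 0.2/0.24 = 0.833 (the article has 0.831). The sample size is n = 2(1.960 + 1.282)²/0.833² = 30.3, so 31 per arm; 0.831 also gives 31. Power at 31 per arm is 90.7% by the normal approximation and 89.8% by the noncentral t. The stated figure reproduces as a single two-sided two-sample comparison.

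**Step 2: group term over four sessions.**
- Expected effect = (0 + 0.2 + 0.2 + 0.2)/4 = 0.15 m/s.
- SD of a patient's four-session mean = σ√((1 + 3ρ)/4).
- Power from the noncentral t with 60 df.
- Example, raw reading, ρ = 0.7: SD = 0.24 × √0.775 = 0.211, d = 0.15/0.211 = 0.71, power 78.5%.

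**Step 3: group-by-session interaction.**
- Sum of squared deviations of the effects (0, 0.2, 0.2, 0.2) from their mean 0.15 = 0.0225 + 3 × 0.0025 = 0.03.
- Noncentrality = (31/2) × 0.03/(σ²(1−ρ)), tested as F(3, 180).
- On the change reading σ²(1−ρ) = 0.24²/2 = 0.0288, so the noncentrality is 16.1 and power 93.1% at every ρ.

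**Step 4: baseline-adjusted ANCOVA at one session.** Residual SD = σ√(1−ρ²), effect 0.2 m/s.

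Power at 31 per arm:

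| ρ | Group term, raw | Group term, change | Interaction, raw | Interaction, change | ANCOVA, raw | ANCOVA, change |
|---|---|---|---|---|---|---|
| 0.2 | 96.9% | 99.8% | 75.5% | 93.1% | 90.9% | 98.6% |
| 0.3 | 94.0% | 98.6% | 81.5% | 93.1% | 92.3% | 97.9% |
| 0.4 | 90.4% | 94.7% | 87.5% | 93.1% | 94.1% | 97.1% |
| 0.5 | 86.5% | 86.5% | 93.1% | 93.1% | 96.1% | 96.1% |
| 0.7 | 78.5% | 56.8% | 99.5% | 93.1% | 99.5% | 93.8% |
| 0.8 | 74.7% | 38.3% | about 100% | 93.1% | about 100% | 92.5% |
| 0.9 | 71.1% | 20.3% | about 100% | 93.1% | about 100% | 91.2% |

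On the raw reading, the group term would need 43 per arm at ρ = 0.7 and 51 at ρ = 0.9 to reach 90%.

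**Step 5: the post-hoc t-tests.** Take the standardised difference used for the sample size, 0.833, at one named session. With Bonferroni over three sessions (0.05/3) power is 79.0%; over four (0.05/4) it is 75.7%. This holds for raw values if 0.24 is a raw SD, and for changes from baseline if 0.24 is an SD of change.

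**The case against.** A reader might infer that the planned ANOVA cannot deliver 90% power. The documents do not support that. The group term keeps 90% up to a correlation of about 0.4. The interaction in the same ANOVA reaches 93% at any correlation if 0.24 is an SD of change, and from about 0.5 upwards if it is a raw SD. The text never says that the group term decides. The lowest figures also need a high correlation together with the change reading: at 0.8 to 0.9 that implies a raw velocity SD of 0.38 to 0.54 m/s, which nothing in the article confirms.

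A reader might also infer that baseline is never used, or that the t-tests compare raw velocities. The interaction does set later sessions against baseline, and the article does not say whether the t-tests use raw values or changes. On changes, with 0.24 as their SD, one t-test at 0.05 would be exactly the comparison that was sized (89.8%), before Bonferroni.

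Nor is this a matter of bias. Randomisation keeps an unadjusted comparison valid; what is lost is efficiency and clarity. The article is condensed and calls the trial early exploratory, and covariates are often left to an analysis plan that is not shown.

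All of this stands and limits the point. It does not remove it, because the treatment of baseline as an outcome session in the ANOVA is stated, not left open. The post-hoc tests do exist to locate the effect, as the other side would say, but under Bonferroni they fall below 90% at the planned SD.

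**Conclusion.** The point holds as a free improvement, not as a fatal error. Baseline sits among the analysed outcome sessions, no adjustment is stated, and the text leaves open whether the group term, the interaction or a t-test at some session answers the primary question. Neither ANOVA route is secure. The group term loses a quarter of a constant effect and falls below 90% once the correlation passes about 0.4. The interaction is below 90% at correlations of 0.4 or less on the raw reading, and where it is well powered it still hands direction and size to t-tests with about 79% power each.

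The baseline-adjusted contrast at 3 months is the only option checked that stays near or above 91% (lowest value 90.9%) from 0.2 to 0.9 on both readings. At high correlation on the change reading its power is close to that of the interaction (92.5% against 93.1% at 0.8). The gain there is a single estimate with direction and size, not extra power.

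These figures rest on compound symmetry, a constant effect after tuning, 31 evaluable patients per arm and an assumed correlation range. If the effect were only 0.1 m/s at tuning, the four-session mean would be (0 + 0.1 + 0.2 + 0.2)/4 = 0.125 m/s, and the group term would lose more power.

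**What to change.** In Statistical Analysis, take baseline out of the response. Analyse post-baseline walking velocity by ANCOVA, or by a mixed model with arm, session and arm-by-session, with baseline velocity as covariate. Name the arm contrast at 3 months, with its 95% confidence interval, as the primary estimate; this agrees with the article's own label for that session. Report the tuning-session and 6-month contrasts as secondary. With one primary contrast, the primary test needs no Bonferroni division. An unstructured covariance and time since stroke as a further covariate are optional.

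The cost is one rewritten paragraph in the protocol or the analysis plan, settled before arms are compared. No new data, visits or patients are needed.

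### A normality test decides the method for the primary outcome, and the fallback for the arm-by-session ANOVA is not a defined test

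*Protocol article*

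**What the plan says.** The Statistical Analysis section covers four sessions (baseline, tuning, 3 months, 6 months) on an intention-to-treat basis. Its aim is given as: "The primary emphasis of the statistical analysis will be on between-group differences to establish if differences in outcome measures are apparent". The method follows: "This will be achieved using two-way repeated measures ANOVA analysis, followed by a series of post-hoc tests which are most likely to be t-tests". Then comes the switching rule: "All data will be tested for normality, and where normality does not occur the equivalent nonparametric tests will be used instead". On error control: "A significance level of 0.05 will be used and a Bonferroni correction will be used when multiple t-tests are required".

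The section on quantitative data states: "The primary outcome measure for this study is walking velocity". Nothing exempts velocity from the switching rule. The sample size section rests on a difference in m/s: "A clinically relevant change in walking velocity has been identified as 0.2 m/s".

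The article does not name the normality test, its level, the quantity tested (raw values, arm-by-session cells, change scores or residuals), the action when some sessions pass and others fail, or the test that replaces the two-way ANOVA.

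**The concern.** A rule that picks the method after a look at the data leaves the primary analysis open until then. Two things are at stake.

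- **The planned test.** The ANOVA has a between-patient factor (arm) and a within-patient factor (session), and it is the tool given for between-group differences. If the fallback is a familiar rank test, the arm-by-session comparison may have no counterpart.
- **The estimand.** The trial is sized on a difference in mean velocity. A rank test addresses a different quantity, so after a switch the main result may no longer speak directly to 0.2 m/s. Sessions of the same outcome could also end up with different tests.

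An article may leave detail to an analysis plan. Here, however, the article itself states the decision rule, and an analysis plan that followed it would inherit the problem.

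**Working it through.** **1. The plan's own figure.** Inputs from the sample size section: difference 0.2 m/s, SD 0.24 m/s, stated standardised difference 0.831 (0.2/0.24 = 0.833), 90% power, 5% level (two-sided assumed).

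n per arm = 2(z₀.₉₇₅ + z₀.₉₀)²/d² = 2(1.960 + 1.282)²/d²

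- d = 0.833: 21.02/0.694 = 30.3, so 31 per arm
- d = 0.831: 21.02/0.6906 = 30.4, so 31 per arm

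The total of 62 reproduces. Exact t-test power at 31 per arm is 89.6–89.8%. This is a calculation for a difference between two means, so the target is a mean difference in m/s.

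**2. How often normal data would trigger a switch.** Assume tests at the 0.05 level. With k independent tests, P(at least one rejection) = 1 − 0.95^k.

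| k | Chance of a rejection |
|---|---|
| 1 | 5.0% |
| 2 | 9.8% |
| 4 | 18.5% |
| 8 (2 arms × 4 sessions) | 33.7% |

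Shapiro-Wilk simulation of eight correlated cells:

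- 35 per arm: 33%, 32% and 31% at correlation 0.5, 0.7 and 0.8
- 31 per arm: 33%, 31% and 26% at correlation 0.5, 0.7 and 0.9

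In the 31-per-arm runs, every simulated trial with a rejection had some cells that passed and some that failed. Skew raises the rate. A single test at 35 per arm rejects about 51% of the time for a gamma distribution with shape 4.

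**3. What the common rank tests would test.**

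| Test | Arm | Session | Arm × session |
|---|---|---|---|
| Planned two-way ANOVA | yes | yes | yes |
| Friedman | no | yes | no |
| Mann-Whitney | yes, one session at a time | no | no |
| Wilcoxon signed-rank | no | yes, two sessions | no |

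Friedman was simulated with 62 patients, between-patient SD 0.20 and within-patient SD 0.13 (√(0.20² + 0.13²) = 0.24).

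- Constant arm difference of 0.2 m/s: rejects 4.6% of the time, its null rate.
- No arm difference, but a common trend of 0, 0.05, 0.10, 0.10 m/s: rejects 96% of the time.

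It therefore cannot stand in for a test of arm.

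**4. Effect on error rates.** Two-group comparison at one time point, 31 per arm, SD 0.24, shift 0.2 m/s for power, 6,000 runs. The two-stage rule uses Mann-Whitney if Shapiro-Wilk rejects in either arm, and the t-test otherwise.

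| Data | Flagged | Type I, t-test | Type I, two-stage | Power, t-test | Power, two-stage |
|---|---|---|---|---|---|
| Normal | about 10% | 4.6% | 4.6% | 90.3% | 90.2% |
| Lognormal, σ = 0.3 | 61–62% | 4.8% | 5.1% | 89.8% | 92.6% |
| Lognormal, σ = 0.5 | 93% | 4.7% | 5.0% | 89.5% | 96.8% |

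The simulation standard error at 5% is √(0.05 × 0.95/6000) = 0.28 percentage points. A separate run with gamma (shape 4) data gave 5.8% for the two-stage rule against 5.2% for the t-test alone. Another set of runs gave 4.6–5.3%.

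**5. What a fixed baseline-adjusted model would give.** For normal data and an assumed baseline correlation of 0.5–0.7, simulated power was 96–99%, against 90% for the two-stage rule. Over four assumed scenarios it was higher in three and about the same in the fourth.

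**The case against.** Much of the case on the other side stands.

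- **Frequency.** A reader might infer that about a third of trials with normal data would switch. The article states no any-cell trigger, no test and no level, and does not say that raw values are tested. If one set of residuals were tested at 0.05, the rate would be about 5%. The 31–33% figure is one scenario.
- **No nonparametric equivalent.** That is too strong. ANOVA-type rank statistics and the aligned rank transform exist for factorial longitudinal data. What the text supports is narrower: the article names none, and the common rank tests do not do the job.
- **Loss of the primary test.** A reader might infer that a switch leaves the primary hypothesis untested. The null in the study design section is no difference in outcomes between the two ways of tuning. A Mann-Whitney test between arms still addresses that, and on change scores it also uses baseline. What could be lost is the planned arm-by-session test.
- **Estimate in m/s.** A rank test does not stop anyone from reporting a mean difference. A Hodges-Lehmann shift is also in m/s, and averaged 0.20 in simulation under a pure shift of 0.2. It need not equal the mean difference when the arms differ in shape, and the article does not say which would be reported.
- **Error rates.** The two-stage rule costs little or nothing in type I error or in power against the t-test. Those who compare the data are to be blinded to arm, which limits any choice of method that favours one arm. The Discussion calls the trial early and exploratory.

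These points limit the harm. They do not fix the method or the estimand in advance, and blinding does not do so either.

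**Conclusion.** The concern holds in a limited form. The rule as stated leaves the method and the estimand for walking velocity to depend on a normality test, and the replacement for the two-way ANOVA is undefined. The sample size arithmetic is sound and needs no change.

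A reader might infer that the false-positive rate is inflated. The checks do not show this: two-stage type I error was 4.6–5.8% over all runs, and the highest value came with 5.2% for the t-test alone on the same data. These error rates apply to a simple two-group comparison, not to the full four-session analysis.

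The size of the problem is the chance of an unplanned change of method. For normal data that is roughly 5% to 33%, depending on the rule actually applied, and it is higher with skew. The Shapiro-Wilk test, the 0.05 level for it, two-sided testing, the session correlations, the skewed distributions and the Friedman trend and variances are all assumptions; the article gives none of them.

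**What to change.** 1. Remove the normality-triggered switch for walking velocity.
2. Name one model in advance for the between-arm difference, reported in m/s with a confidence interval. A baseline-adjusted linear model or a mixed model for repeated measures would serve. This is a new proposal: the article contains no such model, and it would replace or sharpen the ANOVA. The time point of the primary contrast should be named with it.
3. Check residuals descriptively, without a decision rule attached.
4. Add one named robustness analysis of the same difference, a permutation test or a bootstrap confidence interval, run whatever the residuals look like.
5. For the Modified Ashworth Scale, and for the Modified Rivermead Mobility Index if it is treated as ordinal, name a rank or ordinal method in advance.

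The cost is a few sentences and a small amount of analysis work. No extra patients or measurements are needed.
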